#### Control condition

Participants allocated to the control condition will not be explicitly informed that they are control participants. They will be given a leaflet entitled “Alcohol: The Basics” which includes information about alcohol. The leaflet content is *not* expected to be effective at promoting behaviour change
[29].

### Outcomes

#### Primary outcomes

● Change in AUDIT scores between trial recruitment and follow-up.

● Proportion of hazardous and harmful drinkers (scoring 8 or higher on AUDIT) at follow-up.

#### Secondary outcomes

● AUDIT consumption subscale score.

● AUDIT problems subscale score.

● AUDIT dependence subscale score.

● General health status assessed using EQ-5D
[30].

#### Data collection

Additional trial web pages have been developed and incorporated into the existing online system for pharmacists to record trial data
[31]. The research team will have access to trial data by using secure usernames and passwords created for the trial. This online system has several advantages over the paper-pen method. RD will have access to pharmacy participants’ details as soon as each participant is randomised and the visit to the pharmacy completed; this will allow follow-up telephone calls to be made promptly and avoid delays caused by physically collecting completed trial paperwork from pharmacies. Access to randomisation status and baseline data is prevented. The system requires pharmacists to complete all fields correctly before proceeding to the next step, ensuring trial data are complete. Data can also be accessed without revealing randomisation status.

RD will arrange two telephone calls with study participants. During both calls the researcher will be blind to the participants’ intervention condition. The first telephone call will be made within two weeks of recruitment and will take between two to three minutes to complete. The purpose of this call will be to make personal contact to confirm contact details, gather additional tracing information as necessary and to arrange the follow-up study telephone call three-months post randomisation. Structured interview schedules will be used to ensure all participants are asked the same questions in a consistent manner in both calls. The primary and secondary outcomes specified above will be collected in the follow-up study telephone call after three months. This will take approximately 15 minutes to complete and participants will receive £10 gift voucher as a token of appreciation for completing the second call.

#### Randomisation

**Sequence generation** We expect each pharmacist to recruit 24 participants on average over a period of approximately 6 months, with equivalent numbers of intervention (*N* = 12) and control (*N* = 12) participants randomised for each pharmacist. The random sequence was generated in blocks of 12 (BI = 6, Control = 6) with an Excel program, with further blocks of the same size generated for those who recruited more participants.

**Allocation concealment mechanism** Only after the pharmacist has opened a sealed numbered envelope will randomisation status be revealed. Neither pharmacists nor pharmacy support staff will be able to subvert randomisation and choose which participant will receive BI if this process is implemented as designed. This will be monitored during pharmacy visits, when RD will check the sealed envelopes for evidence of tampering and that the envelopes have been opened in numerical order, and also by checking the integrity of the blocks via the online data entry system. In addition, pharmacists will receive training on the importance of following trial procedures.

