**Methods and design:**

This study is a two-arm randomised controlled trial to determine the effectiveness of BI delivered by community pharmacists in their pharmacies. Eligible and consenting participants (aged 18 years or older) will be randomised in equal numbers to either a BI delivered by 17 community pharmacists or a non-intervention control condition. The intervention will be a brief motivational discussion to support a reduction in alcohol consumption and will take approximately 10 minutes to deliver. Participants randomised to the control arm will be given an alcohol information leaflet with no opportunity for discussion. Study pharmacists will be volunteers who respond to an invitation to participate, sent to all community pharmacists in the London borough of Hammersmith and Fulham. Participating pharmacists will receive 7 hours training on trial procedures and the delivery of BI. Pharmacy support staff will also receive training (4 hours) on how to approach and inform pharmacy customers about the study, with formal trial recruitment undertaken by the pharmacist in a consultation room. At three month follow up, alcohol consumption and related problems will be assessed with the Alcohol Use Disorders Identification Test (AUDIT) administered by telephone.

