#### Community pharmacist recruitment

Pharmacists practicing in community pharmacies within Hammersmith and Fulham, with an NHS contract and a private consultation room will be invited to participate. Pharmacists will be contacted initially by letter and telephone. Following this, personal pharmacy visits will be arranged to enable the Chief Investigator (RD) to provide information on the trial, obtain pharmacists’ consent and arrange suitable training dates. A total of 17 pharmacists will be recruited for the study. Pharmacy support staff working with recruited pharmacists will be invited to attend a brief training session on how to inform and identify suitable participants for the trial.

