#### Statistical methods

The data will be analysed on an intention to treat basis. For outcome measures t-tests or Mann–Whitney tests will be used for continuous data and chi-square tests used for categorical data. If possible confounding is identified, ANCOVA and logistic regression will be used to examine the effect of the interventions over and above these other factors, and effect sizes and odds ratios calculated. For all tests, if necessary, measures will be transformed before analysis. All analyses not conforming to an *a priori* statistical plan will be declared as exploratory.

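### Allocation is blocked within each of 17 pharmacists but the stated tests ignore pharmacist: a small loss of precision if the BI effect is common, and an error of uncertain net direction if it varies

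*Protocol article*

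**What the plan says.** **Design.** The abstract has participants "randomised in equal numbers to either a BI delivered by 17 community pharmacists or a non-intervention control condition". Community pharmacist recruitment fixes the number: "A total of 17 pharmacists will be recruited for the study". Randomisation gives the expected load, "We expect each pharmacist to recruit 24 participants on average", and plans 12 BI and 12 control "participants randomised for each pharmacist". On the method it says: "The random sequence was generated in blocks of 12 (BI = 6, Control = 6) with an Excel program". Anyone whose recruitment goes beyond the planned number receives extra blocks, also of 12. Read together, each pharmacist works through separate balanced blocks, which makes pharmacist a stratification factor.

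**Analysis.** Statistical methods states: "t-tests or Mann–Whitney tests will be used for continuous data and chi-square tests used for categorical data". ANCOVA and logistic regression come in only if possible confounding is found. Pharmacist is not named there, nor in Sample size, which is a simple two-group calculation.

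**The concern.** The analysis should follow the randomisation. A two-sample t-test or a plain chi-square test treats the participants as one unstratified sample, whereas allocation was forced to balance within 17 strata. Any difference in mean outcome between pharmacists is then removed from the arm comparison by design but left in the test's error variance.

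The second issue is that the pharmacist delivers the BI after brief training, with freedom in how the discussion topics are used. The Discussion says that pharmacists' capacity to deliver BI effectively is what is being studied. If the BI effect differs between pharmacists, a conclusion about community pharmacists in general carries sampling variation from only 17 of them, and the stated tests do not allow for it. The two issues push the error in opposite directions, so both have to be sized.

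**Working it through.** **Inputs from the protocol article.** Standardised effect 0.30, one-tailed alpha 0.05, 80% power, 139 evaluable per group, 30% attrition, 199 recruited per group (Sample size); 17 pharmacists (Community pharmacist recruitment); 1:1 blocks of 12 per pharmacist (Randomisation).

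**Assumptions, because the document gives no figure.** ICC ρ is the between-pharmacist share of outcome variance, 0.02–0.10. τ is the between-pharmacist SD of the BI effect, 0.10–0.25 in outcome SDs. Outcome SD is 1.

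**1. The plan's own figure.** Normal approximation: n = 2(1.645 + 0.842)²/0.30² = 137.4, so 138. The exact noncentral-t calculation gives 139 (power 0.802). With attrition, 139/0.70 = 198.6, so 199. Both stated figures reproduce.

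**2. Common BI effect (τ = 0).** With balance inside each pharmacist, the true variance of the arm difference is 2(1−ρ)/n. The unadjusted t-test uses about 2/n, so its SE is too large by 1/√(1−ρ).
- Two-sided alpha = 2[1 − Φ(1.96/√(1−ρ))].
- Power with pharmacist in the model, one-sided 5%, n = 139: Φ(0.30/√(2(1−ρ)/139) − 1.645). The same formula at ρ = 0 gives the unadjusted 0.804.

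| ρ | SE too large by | Actual two-sided alpha | Power with pharmacist |
|---|---|---|---|
| 0.02 | 1.0% | 4.8% | 0.811 |
| 0.05 | 2.6% | 4.4% | 0.822 |
| 0.10 | 5.4% | 3.9% | 0.839 |

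A simulation (17 pharmacists, 8 evaluable per arm each, 20,000 runs per scenario, one-sided 5%) agrees. At ρ = 0.10 the t-test's type I error is 0.040. Adding pharmacist brings it to 0.049 and raises power from 0.808 to 0.833.

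**3. BI effect varying between pharmacists.** For inference to pharmacists in general:
- True variance: 2(1−ρ)/139 + τ²/17.
- Variance the t-test expects: 2(1 + τ²/2)/139, because varying effects also widen the observed spread in the BI arm.
- R is the first divided by the second; two-sided type I error = 2[1 − Φ(1.96/√R)].

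Worked case, ρ = 0 and τ = 0.25: true 0.01439 + 0.0625/17 = 0.01807; expected 0.01439 × 1.03125 = 0.01484; R = 1.217; error 7.6%.

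| ρ | τ = 0.10 | τ = 0.20 | τ = 0.25 |
|---|---|---|---|
| 0 | 5.4% | 6.7% | 7.6% |
| 0.05 | 4.8% | 6.1% | 7.0% |
| 0.10 | 4.3% | 5.5% | 6.4% |

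The only sidedness the document states is one-tailed 5%. On that scale the τ = 0.25 figures are 6.8% at ρ = 0 and 6.0% at ρ = 0.10.

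**4. What each remedy does.** In the same simulation with τ² = 0.05 (τ about 0.22), one-sided type I error is:
- plain t-test: 0.058–0.066;
- pharmacist as a main effect: 0.063–0.068, so not cured;
- an analysis of the 17 within-pharmacist differences, which uses the between-pharmacist variation in the effect: 0.048–0.052, with power of about 0.70–0.73.

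**The case against.** *The consequence that follows from the stratification alone is conservative and small.* This stands. No false-positive risk arises from ignoring the strata.

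*The anti-conservative part needs further assumptions.* This also stands. It requires a BI effect that averages zero yet differs between pharmacists, and inference beyond the 17. If BI works for nobody, τ = 0 and there is no inflation. The 17 are volunteers from one borough, and the Discussion leaves national decision-making to a later multi-centre trial, so inference conditional on these pharmacists is defensible. Against that, the Aim is worded for community pharmacists generally.

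*Correlation within pharmacist is not shown.* Correct. The pharmacist administers the baseline AUDIT, which enters the change score, but the follow-up AUDIT is taken by telephone by a blinded researcher. An ICC near zero is possible.

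*The detail may sit in an unseen statistical plan.* Only partly persuasive. The article states which tests will be used, and the complaint is about that choice. The conditional ANCOVA does not fill the gap: its trigger is confounding, and balance within pharmacist makes it unlikely that pharmacist would be identified as a confounder.

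*Two stronger readings are tempting, and the document supports neither.* A reader might infer that 17 groups of about 24 call for a cluster-trial design effect and a larger sample. They do not, because both arms occur within every pharmacist. A reader might also size the inflation as (2/139 + τ²/17)/(2/139), which gives 4–26% extra variance and 5.5–8.0% two-sided error. That omits the variance the t-test itself absorbs and sets the ICC to zero.

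**Conclusion.** The mismatch is real and modest. Allocation is stratified by pharmacist and the stated tests are not. With a common BI effect, the cost is a standard error 1–5% too large for an ICC of 0.02–0.10 and a few points of power at most. If the BI effect varies with SD 0.10–0.25 and the conclusion is meant for pharmacists in general, the errors partly offset: net two-sided type I error runs from 4.3% to 7.6% over the ranges examined, on either side of 5%. Every magnitude rests on an assumed ICC and τ. The point does not invalidate the trial or its 139 and 199 per group. It is a correction that should be made because it makes the analysis follow the allocation at almost no cost.

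**What to change.** **Primary analyses.** State in Statistical methods that they include pharmacist as the stratification factor:
- AUDIT score: ANCOVA of follow-up AUDIT on arm and baseline AUDIT, with a fixed or random pharmacist effect. Using change as the response in the same model gives the same arm effect, so the stated outcome is kept.
- Proportion scoring 8 or higher: the matching logistic model, or a Mantel–Haenszel analysis stratified by pharmacist.

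This recovers the small loss of precision only and gives no protection if the BI effect varies.

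**Sensitivity analysis.** Prespecify a model with a pharmacist-by-arm random effect, and say that it addresses inference to pharmacists in general. State its downside: with 17 pharmacists, power falls to about 0.70–0.73 if the between-pharmacist variance of the effect is 0.05. A non-significant result there should be read with that in mind.

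**Cost.** Wording only. Pharmacists enter trial data online and block integrity is checked through that system, so pharmacist identity should already be recorded. Because the article declares analyses outside the a priori plan exploratory, the change should be made before outcome data are analysed by arm.

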#### Participant recruitment

Pharmacy customers will be informed about the study by pharmacy staff if they are observed performing any of the following activities: a) viewing study posters and flyers displayed within the pharmacy counter area; b) making a general health query or seeking advice which could be linked to alcohol use; c) purchasing pharmacy over the counter products for smoking cessation aids, gastrointestinal remedies, sleep aids and central nervous system depressants (listed in the current edition of the *Medicine Chest* directory
[21] d) receiving any of the following pharmacy services: Smoking Cessation, Medication Use Review, Health Check or Emergency Hormonal Contraception; e) presenting prescriptions for medications for any of the following conditions: cardiovascular disease, depression or anxiety, diabetes or gastric problems.

Records of number of customers informed about the study but who refuse to participate or do not fulfil the study criteria will be kept. Anonymous information on customers’ gender, activity in the pharmacy, reason given for not participating and the date they visited the pharmacy will be recorded. Customers will have the content of the Participant Information Sheet explained by pharmacy staff and be given a copy to keep and be asked a Single Alcohol Screening Question (SASQ), “*How often do you have three or more drinks on a single occasion*?” This question was adapted for this trial and is based on the previously validated SASQ
[22,23]. We are aware that such brief screeners have their limitations and thus we used a two stage eligibility procedure
[24]. Customers who are administered the SASQ and report consuming three or more drinks monthly or more regularly will be invited to have their alcohol use assessed further using the AUDIT by the pharmacist in the consultation room. Participants who fulfil the study criteria and are willing to participate in the trial will sign two copies of the consent form with the pharmacist in the consultation room and will be given one copy to keep.

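### Fixed blocks of 12 within each pharmacist let the recruiter foresee the end of a block if the block size is known or inferred, so the assurance against subversion is too strong

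*Protocol article*

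**What the plan says.** The Randomisation section of the protocol article describes the sequence: "The random sequence was generated in blocks of 12 (BI = 6, Control = 6", "with further blocks of the same size generated for those who recruited more participants". Balance is set within the recruiter: equal numbers of BI and control "participants randomised for each pharmacist". On volume it says: "We expect each pharmacist to recruit 24 participants on average over a period of approximately 6 months". Community pharmacist recruitment adds: "A total of 17 pharmacists will be recruited for the study".

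The pharmacist controls entry. The abstract has "formal trial recruitment undertaken by the pharmacist in a consultation room". Under Participant recruitment, pharmacy staff ask the first screening question, but the pharmacist administers the AUDIT in the consultation room and takes consent there: "Participants who fulfil the study criteria and are willing to participate in the trial will sign two copies of the consent form". The pharmacist then opens the numbered envelope and delivers the allocated condition.

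Under Allocation concealment mechanism the article gives this assurance: "Neither pharmacists nor pharmacy support staff will be able to subvert randomisation and choose which participant will receive BI". The sentence makes this conditional on the process being carried out as planned. Monitoring looks for tampering, for envelopes opened out of order, and for blocks that are not intact in the online system.

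**The concern.** Sealed envelopes hide an allocation only while it cannot be worked out from earlier ones. Here one person decides who is eligible, obtains consent and has seen every earlier allocation in a private sequence of constant block size. Once six of one arm have been used, the rest of that block is settled.

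Foreknowledge matters at two points:

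- **Who enters.** A borderline AUDIT (near 8 or 20), or the effort put into obtaining consent, could vary with the expected allocation. The two conditions differ in burden: about 10 minutes of discussion against handing over a leaflet. The Discussion section acknowledges that pharmacists are short of time.
- **The baseline score.** The pharmacist's AUDIT is the baseline for the first primary outcome, change in AUDIT. The Blinding section removes pharmacists from data collection only after the envelope is opened, so it does not cover this step.

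The second primary outcome, the proportion scoring 8 or more at follow-up, is planned as a chi-square comparison, with adjustment only if confounding is identified. Selective entry could pass directly into it.

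**Working it through.** **Inputs from the article.** Block size 12, six per arm; later blocks the same size; blocks kept within pharmacist; 17 pharmacists; 24 recruits each on average; total 398 (target) or 408 (projected yield, Sample size section).

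**The article's own figure.** 408/17 = 24.0 and 398/17 = 23.4, which agrees with the stated average of 24, or two full blocks. At 408 this gives 17 × 2 = 34 blocks. The article states no figure for predictability.

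**Certain allocations per block.** An allocation is certain when every place left in the block, including its own, belongs to one arm. With r places left, the probability is 2 × C(12 − r, 6) / C(12, 6), where C(12, 6) = 924:

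| Place in block | r | Probability certain |
|---|---|---|
| 12th | 1 | 924/924 = 1.000 |
| 11th | 2 | 420/924 = 0.455 |
| 10th | 3 | 168/924 = 0.182 |
| 9th | 4 | 56/924 = 0.061 |
| 8th | 5 | 14/924 = 0.015 |
| 7th | 6 | 2/924 = 0.002 |
| 1st to 6th | 7 to 12 | 0 |

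The sum is 1584/924 = 12/7 = 1.714 per block, or 1/7 = 14.3%. Enumerating all 924 sequences gives the same value. At least two allocations are certain in 45% of blocks and at least three in 18%.

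**Trial-wide, all blocks completed.** 34 × 1.714 = 58 of 408. At the target of 398, 398/7 = 57. Per pharmacist it is 2 × 1.714 = 3.43 of 24.

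**When a pharmacist stops mid-block:**

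| Recruits | Expected certain | Share |
|---|---|---|
| 18 | 1.71 | 9.5% |
| 20 | 1.73 | 8.7% |
| 23 | 2.43 | 10.6% |
| 24 | 3.43 | 14.3% |
| 30 | 3.43 | 11.4% |

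A pharmacist who recruits six or fewer has none.

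**Best guess from a tally.** Always guess the arm used less so far, and toss a coin when level. The expected number correct per block of 2m is m + 4^m / (2 × C(2m, m)) − 1/2. With m = 6 this is 6 + 4096/1848 − 0.5 = 7.716 of 12, or 64.3%. This needs a running count, not the block size.

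**Other fixed sizes.** The certain share for a block of 2m is 1/(m + 1): 33% at size 4, 25% at 6, 20% at 8, 16.7% at 10 and 14.3% at 12.

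**Randomly mixed sizes.** Simulated over 24 recruits, with an observer who knows the set of sizes but not the draw:

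| Sizes | Certain | Best guess correct |
|---|---|---|
| 12 only | 14.2% | 64.4% |
| 4, 6, 8 | 2.2% | 67.3% |
| 8, 10, 12 | 2.0% | 63.8% |
| 6, 8, 10, 12 | 1.1% | 64.4% |

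Mixing removes most of the certainty and leaves the best-guess rate about where it was.

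**The case against.** The strongest reply is that the 14% is conditional. Nothing in the article says pharmacists are told the block size, and a condensed article need not say that it was withheld. The figure also needs someone to keep count and blocks to be completed, while 24 is only an average. This stands: a reader might infer that one allocation in seven is simply known to the pharmacist, and the document does not support that.

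Several further points have weight:

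- **The assurance is conditional too.** A reader might take it as an absolute claim. But the condition does not answer the problem, because foreseeing the next envelope is compatible with intact envelopes opened in order and with correct 6:6 blocks. All three checks would pass.
- **Twelve is comparatively protective.** A reader might infer that the block is too small, but a shorter fixed block would be worse. The weakness is a constant size held by one unblinded recruiter.
- **Other safeguards exist.** Refusals and ineligible customers are recorded with reason and date, the online system requires complete fields before the next step, and follow-up is blinded. The records would allow a later check, though none is stated. Blinded follow-up does not protect selection at entry.
- **Incentives are mixed.** Pharmacists receive a fee for each participant, with no difference by arm stated. That favours enrolling whatever the next allocation.
- **Bias is not sized.** The calculation measures predictability, and nothing in the document converts it into a shift in either primary outcome. A reader might infer that subversion occurred, but there is no evidence of that.

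**Conclusion.** The point holds in conditional form. Constant blocks of 12 within a pharmacist who assesses eligibility, takes consent and sees every allocation make part of the sequence foreseeable without any breach of procedure. If the pharmacist knows or infers the size and keeps a tally, the expected certain share is 14.3% in completed blocks. It is about 9 to 11% in the mid-block cases worked above (18 to 30 recruits). The assurance that pharmacists cannot choose who receives BI is therefore stronger than the design supports. Whether foreknowledge arose, and how much bias would follow, cannot be told from the document. This is an avoidable weakness that is worth correcting; it does not by itself invalidate the comparison.

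**What to change.** 1. For envelopes not yet used, regenerate each pharmacist's sequence in permuted blocks of randomly mixed, undisclosed sizes (for example 6, 8, 10 and 12), still stratified by pharmacist. This takes certain allocations from 14% to about 1%, even for an observer who knows the set of sizes. It does not reduce the best-guess rate of about 64%.
2. Require the AUDIT and consent entries to be locked and time-stamped online before the envelope is opened, and check those times against the allocation entry. This guards against changes after opening. It does not prevent selective effort beforehand.
3. Qualify the assurance under Allocation concealment mechanism: sealed envelopes and the listed checks address tampering and order, not prediction from earlier allocations.
4. The article describes the sequence as already generated, so some or all envelopes may have been used. For those, compare baseline AUDIT, and the refusal and ineligibility records, by position in the block, and report the result.

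The cost is re-packing unused envelopes, a small addition to the online system, and small departures from 12 and 12 per pharmacist.
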